#### 5.3.2 Placebo

Placebo consisting of starch with no active ingredients will be made by the same manufacturer to match the FZHFZY granules as closely as possible, in terms of their colour, appearance, and smell. The colour will be made identical by adding artificial pigment whilst the taste will be adjusted by adding a medicine intermediate. The administration instructions and precautions for the FZHFZY formula and placebo will be identical.

#### 5.3.3 Co-intervention

Patients in each group will be required to apply 10% urea cream topically on their psoriasis lesions twice a day following the fingertip unit (FTU) method [43]. One FTU is measured as the amount (about 0.5 grams) of medication that covers from the tip of an adult finger to the first crease and it is sufficient to cover both sides of an adult. Participants will be instructed to apply the cream immediately after CHM bath therapy, when the skin is still moist. The dosage can be adjusted from its initial dose at the participants' discretion and as their symptoms change. Participants will stop

using the cream for 12 hours before collecting Skin microbiota.

#### 5.3.4 Rescue therapy

Cetirizine hydrochloride tablets will be provided as an additional management for unbearable itch caused by psoriasis.

#### 5.3.5 Trial duration

The trial period is 20 weeks, including an 8-week treatment phase and a 12-week follow-up phase.

### 5.4 Data collection

Eligible participants will be asked to attend an in-person assessment appointment at the dermatology outpatient clinic of GPHCM at eight points: week 0, week 2, week 4, week 6, week 8, week 12, week 16 and week 20. The detailed events and schedule could refer to the Table 1.

#### 5.4.1 Clinical data collection

Data will be collected and recorded in the case report forms (CRF). Participants will be required to record a home diary.

##### 5.4.1.1 Baseline data

- Demographics: Date of birth, age, sex, ethnicity, nationality, marital status, education level, height, abdominal circumference, weight, occupation, long-term residence
- Vital signs: Heart rate, body temperature, respiratory rate and blood pressure
- History of allergy: History of allergy to drugs, food or contact
- Diseases and treatment history: Psoriasis incidence and family history, past treatment history and other diseases and treatment history
- Chemical examinations: Complete blood count, urinalysis, hepatic and renal functions, and Electrocardiograms
- PASI, BSA, 7-point sPGA, itch VAS, DLQI and Skindex-16
- Physical examinations

##### 5.4.1.2 Outcome measures and visits

- PASI, BSA, sPGA and itch VAS: Participants will be evaluated these measures at week 0, 2, 4, 6, 8, 12, 16 and 20
- DLQI and Skindex-16: Evaluate these measures at week 0, 8, and 20
- 11-point ordinal scale: Evaluate it at week 8 and 20
- Blinding credibility: Evaluate it at week 8 and 20
- Chemical examinations: Evaluate electrocardiograms at the baseline, and collect blood (two 4 ml-EDTA tubes and two drying tubes) and urine (one 10 ml-urine tube) at week 0, 8 and 20
- Photos taken for representative skin lesions: Conduct it at each visit
- Concomitant medication, and AEs: Record it during the whole trial phase

- Dispense and collect trial drugs: Dispense trial drugs at week 0, 2, 4, and 6; collect trial drugs at week 2, 4, 6 and 8
- Dispense and collect home diary record sheet: Dispense it at week 0, 2, 4, 6, 8, 12, and 16; collect it at week 2, 4, 6, 8, 12, 16 and 20

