| 7-point sPGA                                           |                                | X                                                                                  | X      | X      | X      | X      | X                                                                                   | X       | X       |

|                                         |  |                                                                                    |   |   |   |   |   |   |   |
|-----------------------------------------|--|------------------------------------------------------------------------------------|---|---|---|---|---|---|---|
| Itch VAS                                |  | X                                                                                  | X | X | X | X | X | X | X |
| DLQI                                    |  | X                                                                                  |   |   |   | X |   |   | X |
| Skindex-16                              |  | X                                                                                  |   |   |   | X |   |   | X |
| Data collection: safety assessment      |  |                                                                                    |   |   |   |   |   |   |   |
| Vital signs                             |  | X                                                                                  |   |   |   | X |   |   | X |
| Physical examination                    |  | X                                                                                  |   |   |   | X |   |   | X |
| Blood test, Urine test                  |  |                                                                                    |   |   |   | X |   |   | X |
| Reporting AEs                           |  | [figure not shown] |   |   |   |   |   |   |   |
| Data collection: feasibility assessment |  |                                                                                    |   |   |   |   |   |   |   |
| Trial medication usage check            |  |                                                                                    | X | X | X | X |   |   |   |
| Blinding credibility                    |  |                                                                                    |   | X |   | X |   |   | X |
| Acceptability                           |  |                                                                                    |   |   |   | X |   |   | X |

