## 5.2 Randomisation and Blinding

A total of 60 eligible participants will be randomly assigned at a 1:1 ratio to one of the two groups at the baseline visit. The equal randomisation will be conducted by the staff at the Key Unit of Methodology in Clinical Research (KUMCR) of the GPHCM who is independent of the trial investigators. Only the person has access to the results of randomised allocation. The random allocation sequence will be generated through the blocked randomisation method using the SAS software (version 9.2, SAS Institute, Inc., Cary, NC, USA). Then the randomisation code corresponding to the trial medications will be released by the Interactive Web Response System for Chinese Medicine Trials that is a verified online randomisation facility established by the KUMCR (<http://59.42.21.236:8088/randomisation/portal/portalLogin>). Therefore, the allocation concealment will be ensured.

The participants, trial investigators, outcome assessors, the statistician, and the pharmacist who dispense medications will be blinded to the allocation. The randomisation code can be broken if the appropriate management of the patient in medical emergencies necessitates knowledge of the treatment randomisation. It should be applied by the trial investigator through the online randomisation system and then the principal investigator will be notified to approve of breaking the code. Therefore, the type of trial medications (CHM or placebo) will be identified. In addition, the reason, date, and result of breaking the randomisation code will be recorded in the patient's case report form. Any condition resulting in an unblinding event will report to the ethics committee of the GPHCM. Breaking the randomisation code under medical emergencies should not spread to ensure the clinical trial continues. If a patient's treatment is unblinded by the investigator, the patient will be withdrawn from the study.

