## 5.5 Termination and withdrawal

If participants are diagnosed with other type psoriasis (erythrodermic psoriasis, psoriatic arthritis, or pustular psoriasis) or suffer from serious adverse events during the trial, the study will be terminated. In addition, participants have the right to withdraw from the study at any time for any reason. Trial investigators can receive feedback on trial medications from these participants and ask them to complete the relevant examinations, which will help the researcher to collect data and benefit the care of participants' health.

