## 5.6 Outcome measures

### 5.6.1 Trial feasibility

- The proportion of involvement by the number of screened, eligible and consenting participants, as well as the time requirement to recruit eligible participants will be used to assess the feasibility of the study setting, eligible criteria and recruitment strategies
- The compliance rate of using trial medications and the acceptability question will be used to quantitatively evaluate the feasibility and acceptability of the trial [44]
- Blinding credibility at week 4, week 8 and week 20
- Determine the primary outcome and provide data for sample size calculation in the full-scale trial

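### The acceptability question is scheduled only at weeks 8 and 20, so participants who leave the trial before week 8 have no scheduled rating and the acceptability result may be too favourable

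*Protocol*

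**What the plan says.** Section 5.6.1 of the protocol rests quantitative acceptability on two measures: "The compliance rate of using trial medications and the acceptability question will be used to quantitatively evaluate the feasibility and acceptability of the trial". Section 5.4.1.2 gives the timing of the rating: "11-point ordinal scale: Evaluate it at week 8 and 20". In Table 1 the row "Acceptability" is marked at the same two visits and no others, and the table has no column for early withdrawal.

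Section 5.4.1.2 does not say by name that the 11-point scale is the acceptability question, but the link is well supported. The weeks match the Table 1 row, and the section lists no other acceptability item. The reference cited for the question in 5.6.1 compares single-question measures of patient satisfaction, and section 6.2 refers to satisfaction scores from the pilot. Even without this link, the Table 1 row alone fixes weeks 8 and 20.

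On withdrawal, section 5.5 says that "participants have the right to withdraw from the study at any time for any reason", and then: "Trial investigators can receive feedback on trial medications from these participants and ask them to complete the relevant examinations". The rating is not named there. The qualitative interviews take only people who completed the pilot (synopsis and section 6.1).

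**The concern.** Exploring acceptability is a stated objective (section 3.2). The regimen is a daily home bath of 15 to 20 minutes for eight weeks (section 5.3.1.1), so it is plausible that some people who find it unacceptable leave the trial during those weeks. As written, the plan schedules no rating from them, and the interviews exclude them as well. If early leavers are less satisfied than those who answer, the score is tilted upwards, and the full-scale trial would be designed on too favourable a picture of the regimen.

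The gap is in data collection, which the protocol fixes. An analysis plan can say how missing scores are handled, but it cannot recover answers that were never requested. Table 1 shows no acceptability score before week 8 from which a leaver's view could be predicted.

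**Working it through.** **Inputs from the protocol**
- Randomised: 60, allocated 1:1 (section 5.2).
- Loss to follow-up: 15%, with a minimum pilot size of 50 (section 5.9.1). How the loss splits before and after week 8 is not given.
- Rating visits: weeks 8 and 20 (section 5.4.1.2 and Table 1).
- Trial length: 20 weeks, of which 8 are treatment (section 5.3.5).

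**Input not in the protocol (assumed)**
- Gap g = mean score of answerers minus the mean score that early leavers would have given. Range taken: 0 to 3 points, with -1 to show the reverse case.

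**Step 1. The plan's own figure.** 50 / (1 - 0.15) = 58.8, rounded up to 59. The cruder 50 x 1.15 = 57.5 rounds up to 58. Both agree with the planned 60 to within 2 participants. The sample size is not in question. The protocol states no figure for acceptability itself.

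**Step 2. How many ratings could be missing.** 60 x 0.15 = 9, leaving 51. Nine is the upper limit for leavers before week 8 under the planned loss, because the 15% covers the whole trial. Anyone lost between weeks 8 and 20 already has a week 8 rating.

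**Step 3. Bias of a mean over answerers.** Let d be the share of all randomised who leave before week 8 without answering.

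Mean over everyone = (1 - d) x (answerers' mean) + d x (leavers' mean)

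Bias = answerers' mean - mean over everyone = d x g

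| Share of the 15% lost before week 8 | d | g = -1 | g = 0 | g = 1 | g = 2 | g = 3 |
|---|---|---|---|---|---|---|
| None | 0 | 0 | 0 | 0 | 0 | 0 |
| Half | 0.075 | -0.075 | 0 | 0.075 | 0.15 | 0.225 |
| All | 0.15 | -0.15 | 0 | 0.15 | 0.30 | 0.45 |

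**Step 4. What asking at withdrawal would gain.** Take the extreme row (d = 0.15, g = 3). If all leavers answer, the bias is 0. If half answer, leavers make up 0.075 / 0.925 of the answers. The observed mean is then 3 x 0.075 / 0.925 = 0.243 below the stayers' mean, while the mean over everyone is 0.15 x 3 = 0.45 below it. The remaining bias is 0.45 - 0.243 = 0.207, less than half of 0.45.

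**The case against.** The strongest reply has four parts.

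- **Stopping the bath is not leaving the trial.** A reader might infer that everyone who gives up bathing is lost to the acceptability score. The protocol does not support that. Section 5.3.1.2 tells participants to suspend or discontinue the bath in several situations without ending their participation, and those who still attend are asked at weeks 8 and 20. This stands and narrows the point to people who leave the study before week 8.
- **Section 5.5 already offers a route.** A reader might infer that leavers never give a rating. That goes too far, because "Trial investigators can receive feedback on trial medications from these participants". This stands as a correction of wording. It does not close the gap: the provision is permissive, concerns the medication, and names neither the rating nor the reason for stopping.
- **The other quantitative measure is less exposed.** Medication use is checked at weeks 2, 4, 6 and 8 (Table 1), so early leavers who attend any of these visits contribute to compliance. This stands. Compliance counts use, however, and is not a rating of acceptability.
- **No upward bias is shown.** People may leave for reasons unrelated to the regimen, and the documents give no scores for leavers. This stands.

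It is also fair to say that detailed handling of missing scores, denominators and worst-case bounds may sit in a statistical analysis plan that is not shown. Their absence here is not a fault.

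**Conclusion.** The point holds as a limited, inexpensive improvement to data collection. The protocol does not provide for a rating from those who leave before week 8, so the acceptability result may be too favourable. Under the planned 15% loss and an assumed gap of 0 to 3 points, the shift lies between 0 and 0.45 points. The top of that range needs all nine losses to fall before week 8, none of the nine to answer, and leavers to score 3 points lower. A gap of -1 reverses the sign, to -0.15 at most.

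Three stronger conclusions are not supported. That the result is overstated cannot be asserted, since neither the timing of the loss nor leavers' satisfaction is known. A change in the percentage satisfied cannot be calculated, because the protocol sets no cut-off on the scale. A biased comparison between arms cannot be claimed either, because the protocol states no between-arm analysis of acceptability.

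**What to change.** 1. In Table 1 and section 5.4.1.2, schedule the question at weeks 8 and 20, or at withdrawal if that comes earlier, with a telephone answer allowed. In the same place, state that the 11-point scale is the acceptability question.
2. In section 5.5, state that every willing withdrawn participant is asked this question together with the reason for stopping.
3. In section 5.6.1, commit to reporting the number who answered out of all randomised. Further detail can go in the statistical analysis plan.

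The cost is a line or so in each place and one extra question with a reason at withdrawal. Section 5.5 already foresees contact with leavers, but only as an option, so making the question routine adds some work. Some leavers will still decline or be unreachable, and the reported figure may be less favourable. No treatment rule changes.

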#### 5.4.2 Data collection of biological specimens

After obtaining informed consent from patients, we will collect the biological specimens including blood, urine and stool, skin microbiota and oral cavity microbiota during the trial. All collected specimens will be de-identified to protect patients' privacy unless required by law. These specimens will be stored in the GPHCM for 10 years after the end of the study and will be disposed after the preservation period. Patients have the right to request to dispose the unused biological specimens during the preservation period. These specimens may be used to explore the mechanism of psoriasis in the future and tested in different laboratories as needed. If we want to use these specimens, we will re-submit the ethics application to the Ethics Committee of GPHCM. These specimens can be used after getting the ethics approval.

##### 5.4.2.1 Time to collect biological specimens

- Biological specimens: collect blood (two 5 ml-EDTA tubes and two 5 ml-procoagulant tubes), urine (one 10 ml-urine tubes) and skin microbiota (four microtubes) at week 0, 8 and 20; collect blood (one 2.5 ml-BD tube), stool (two stool tubes) and oral cavity microbiota (two microtubes) at week 0.

**Table 3** Collecting and storing biological specimens

| Biological specimens   | Type                   | Tubes | Time             | T/°C              | Storage                   | Objectives                         |
|------------------------|------------------------|-------|------------------|-------------------|---------------------------|------------------------------------|
| Blood                  | Serum                  | 10    | Week 0, 8 and 20 | -80               | Refrigerator              | Proteomics and metabolomics        |
|                        | PBMC                   | 5     |                  | From -160 to -196 | Liquid nitrogen container | Single-cell flow mass spectrometry |
| Urine                  | Urine supernatant      | 10    |                  | -80               | Refrigerator              | Metabolomics                       |
| Skin microbiota        | Skin microbiota        | 4     |                  | From -160 to -196 | Liquid nitrogen container | Skin microflora                    |
| Blood                  | RNA of whole blood     | 1     | Week 0           | -80               | Refrigerator              | Immune omics                       |
| Stool                  | Stool                  | 2     |                  | -80               | Refrigerator              | Gut microbiota                     |
| Oral cavity microbiota | Oral cavity microbiota | 2     |                  | From -160 to -196 | Liquid nitrogen container | Oral microflora                    |

## 5.5 Termination and withdrawal

If participants are diagnosed with other type psoriasis (erythrodermic psoriasis, psoriatic arthritis, or pustular psoriasis) or suffer from serious adverse events during the trial, the study will be terminated. In addition, participants have the right to withdraw from the study at any time for any reason. Trial investigators can receive feedback on trial medications from these participants and ask them to complete the relevant examinations, which will help the researcher to collect data and benefit the care of participants' health.

## 5.6 Outcome measures

### 5.6.1 Trial feasibility

- The proportion of involvement by the number of screened, eligible and consenting participants, as well as the time requirement to recruit eligible participants will be used to assess the feasibility of the study setting, eligible criteria and recruitment strategies
- The compliance rate of using trial medications and the acceptability question will be used to quantitatively evaluate the feasibility and acceptability of the trial [44]
- Blinding credibility at week 4, week 8 and week 20
- Determine the primary outcome and provide data for sample size calculation in the full-scale trial

### 5.6.2 Efficacy outcomes

#### 5.6.2.1 Primary outcome

- Mean change in the PASI total score from baseline to week 8 and week 20 respectively [45]

#### 5.6.2.2 Secondary efficacy outcomes

- The PGA response, defined as a PGA score of 0 (clear) or 1 (almost clear) and a decrease from baseline at least 2 points on the 7-point static PGA at week 8 and week 20 respectively [46]
- The percentage of patients who achieve at least 75% improvement in PASI score from baseline (PASI-75) to week 8 and week 20 respectively [47]
- The percentage of patients who achieve at least 50% improvement in PASI score from baseline (pasi-50) to week 8 and week 20 respectively [47]
- The mean change in the percent of total BSA affected by psoriasis from baseline to week 8 and week 20 respectively [45]
- The mean change in the total itch VAS from baseline to week 8 and week 20 respectively [48]
- The mean change in the DLQI total score from baseline to week 8 and week 20 respectively [49]
- The mean change in the Skindex-16 total score from baseline to week 8 and week 20 respectively [50]
- The relapse rate at week 20, defined as loss of 50% of PASI improvement from baseline in patients who achieve PASI-50 at week 8 [51].

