#### 5.1.2 Exclusion criteria

- Currently are pregnant and lactating patients
- Currently have uncontrolled or severe diseases, such as cardiovascular, respiratory, digestive, urinary, haematological or psychiatric diseases; have any known malignancy or a history of malignancy
- Are allergic to the medications used in this study
- Currently are participating in or have participated in other clinical trial(s) in the previous month
- Not complete a wash-out period of psoriasis therapies (see Table 2 for detailed washout requirements of each therapy).

**Table 2** Psoriasis therapies and washout requirements.

| Therapies                                                                                                                                                                                                                                                                                                                                                                                                                                                 | Washout requirements |
|-----------------------------------------------------------------------------------------------------------------------------------------------------------------------------------------------------------------------------------------------------------------------------------------------------------------------------------------------------------------------------------------------------------------------------------------------------------|----------------------|
| Topical agents: Glucocorticoids, Calcineurin inhibitors (e.g. Tacrolimus, Pimecrolimus), Vitamin D analogues (e.g. Calcipotriol, Tacalcitol), Retinoids (e.g. tazarotene), combination treatments (eg. Compound Clobetasol Propionate, Carpotriol betamethasone), Keratin promoter (e.g. 2% – 5% coal tar, 3% salicylic acid, 0.1% – 0.5% anthralin, 5% ichthammol), Keratolytic (e.g. 5% – 10% salicylic acid, 0.1% Retinoids), anthralin, and so on [7] | Two weeks            |
| Antimicrobials; Systemic nonbiologic therapies: methotrexate, cyclosporine, acitretin, azathioprine, leflunomide, Mycophenolate Mofetil and so on; Phototherapies: NB-UVB, PUVA, 308 Excimer                                                                                                                                                                                                                                                              | Four weeks           |

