### 5.9.2 Quantitative data analysis

Statistical analysis will be performed in a blinded manner by qualified statisticians using PASW Statistics 25.0 (IBM SPSS Inc., Armonk, New York, USA). All statistical tests are two-sided with a  $P$  value of  $<0.05$  being considered statistically significant.

Efficacy analyses will be based on the intention-to-treat (ITT) population and safety analyses will be based on the safety analyses set population, both of them defined as all randomised patients who received at least one dose of study treatment and the data of at least one visit. Missing data will be replaced using the multiple imputation method for ITT analysis. For the outcome variables, continuous data (e.g. mean change in PASI score, BSA, itch VAS, and DLQI) will be summarised as mean and standard deviation (data with normal distribution) or mean and interquartile range (data without normal distribution), and categorical data (e.g. PASI-50, PASI-75, and relapse rate) will be summarised as counts and percentages. The primary analyses for primary and secondary outcome variables will be based on the ITT population approach, using data collected at baseline, week 8 and week 20.

When outcome variables are continuous data, using an independent  $t$ -test (data with normal distribution) or Mann-Whitney  $U$  test (data without normal distribution) compares the difference between two groups. When outcomes variables are categorical data, using the Chi-squared test (total samples  $\geq 40$  and expectation  $\geq 5$ ) or Fisher's exact test (total samples  $<40$  or expectation  $<1$ ) compares the difference between the two groups. The efficacy outcomes will be assessed by a generalised linear mixed model for repeated measures.

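### Relapse is judged at week 20 only, so a responder who loses the benefit at week 12 or 16 and has regained it by week 20 counts as not relapsed

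*Protocol*

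**What the plan says.** Section 5.6.2.2 defines the outcome as "The relapse rate at week 20, defined as loss of 50% of PASI improvement from baseline in patients who achieve PASI-50 at week 8". The synopsis gives the same definition.

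Section 5.9.2 states that the primary analyses of the primary and secondary outcomes are run "using data collected at baseline, week 8 and week 20".

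The visit schedule in 5.4.1.2 is fuller: "PASI, BSA, sPGA and itch VAS: Participants will be evaluated these measures at week 0, 2, 4, 6, 8, 12, 16 and 20". The same section adds "Concomitant medication, and AEs: Record it during the whole trial phase". Table 1 agrees on both.

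On the period after week 8:

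- Section 5.3.5 says "The trial period is 20 weeks, including an 8-week treatment phase and a 12-week follow-up phase". Trial drugs are collected for the last time at week 8.
- Other psoriasis therapies are restricted only as an entry condition: section 5.1.2 excludes patients who did "Not complete a wash-out period of psoriasis therapies".
- The only rescue treatment named is in 5.3.4: "Cetirizine hydrochloride tablets will be provided as an additional management for unbearable itch caused by psoriasis".
- No section links concomitant medication to relapse or to any other efficacy outcome. Multiple imputation in 5.9.2 is for missing values only.

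**The concern.** Relapse is the only outcome in the protocol devoted to loss of response after treatment ends. It is read at one visit, 12 weeks after the last dose, although two intermediate visits supply the same score. The rule does not consider what happened between those points.

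A patient whose psoriasis returns early is a plausible candidate for other treatment before week 20. If that treatment works, the week-20 PASI reflects the new therapy, and the patient enters the table as a durable responder. A loss of response that resolves by itself before week 20 is counted in the same way.

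Two things are at stake. The relapse rate may be too low as a description of what happens after the baths stop. The arm comparison may also be off if one arm is re-treated more often or more successfully than the other. Section 5.6.1 wants the pilot to help choose the primary outcome and supply sample-size data for the full trial, so a distorted rate could carry forward.

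**Working it through.** **Plan's own figure.** The protocol gives no expected relapse rate, effect size or power for relapse, so there is nothing to reproduce on this point. The overall sample size is consistent with its stated basis: 50/(1 − 0.15) = 58.8, which rounds up to 59, or 60 with equal arms. It does not bear on relapse.

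**The rule as a formula.** With B the baseline PASI, W the week-8 PASI and X the week-20 PASI:

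- Responder: (B − W)/B ≥ 0.5.
- Relapse: (X − W)/(B − W) ≥ 0.5, reading the definition as a loss of at least 50%. The equivalent threshold is X ≥ W + 0.5 × (B − W).

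Weeks 12 and 16 do not appear.

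**One assumed patient.** Take B = 8.0 and W = 3.0.

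- Improvement is 5.0/8.0 = 62.5%, so the patient is a responder. The threshold is 3.0 + 0.5 × 5.0 = 5.5.
- Week 12 PASI is 6.5: (6.5 − 3.0)/5.0 = 70% of the improvement lost.
- The patient then starts another therapy, or remits. If week 20 is 4.0, then (4.0 − 3.0)/5.0 = 20% lost, scored as not relapsed.
- If week 20 is instead 6.0, then (6.0 − 3.0)/5.0 = 60% lost, scored as relapsed. The patient is missed only when the week-20 value has returned below 5.5.

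**Effect on a rate (all inputs assumed).** Let f be the true proportion of responders losing at least half the improvement at any follow-up visit, and m the share of those back below the threshold at week 20. The recorded rate is f × (1 − m). With 15 responders in an arm, 6 of whom relapse, f = 6/15 = 40%:

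| m | Expected count | Recorded rate |
|---|---|---|
| 0 | 6 | 40% |
| 25% | 4.5 | 30% |
| 50% | 3 | 20% |

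**Effect on the arm comparison (all inputs assumed).** Let s be the share of relapsers re-treated and r the share of those restored, so m = s × r.

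- True rate 60% in both arms; s = 50% in one arm and 25% in the other. At r = 50% the recorded rates are 0.60 × 0.75 = 45% and 0.60 × 0.875 = 52.5%, a false difference of 7.5 points. At r = 100% they are 30% and 45%, a false difference of 15 points.
- True rates 60% (control) and 40% (herbal), a difference of 20 points. With s = 50% in both arms and r = 100%, the rates read 30% and 20%, a difference of 10 points. With s = 50% in control, 25% in herbal and r = 100%, both read 30% and the difference vanishes. With those shares reversed, the rates read 45% and 20%, a difference of 25 points.

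Depending on inputs the protocol does not supply, the comparison can therefore shrink, disappear, widen or arise from nothing.

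**The case against.** The strongest defence is that status at week 20 is a coherent quantity. It asks whether the benefit has gone 12 weeks after treatment, and it matches the other efficacy outcomes, all read at weeks 8 and 20. A patient who flares at week 12 and has remitted by week 20 is correctly not in relapse on that measure. This stands, and it is why the week-20 status should be kept. A reader might infer that the definition is an outright error. The documents do not support that: the choice is defensible but incomplete for judging loss of response during follow-up.

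Second, how to handle PASI values observed after new therapy is commonly left to the SAP, which is not shown. This stands in part. Silence on re-treatment alone would be no finding. But the protocol itself fixes the relapse visit and the analysis visits, and an SAP would have to depart from 5.6.2.2 and 5.9.2 to count a loss at week 12 or 16. The generalised linear mixed model in 5.9.2 names no visits, and it does not change the relapse definition.

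Third, the illustration rests wholly on assumption, and relapse is assessed in a subgroup of a 60-patient pilot. At 6 of 15 the exact 95% interval is 16% to 68%, so a shift of 10 to 20 points lies within sampling error. This stands and limits the severity.

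Fourth, using the therapies in Table 2 as a re-treatment trigger would misclassify. The table includes antimicrobials, which may be given for an unrelated infection, and it does not name Chinese herbal medicine. This stands, and the fix below avoids that list.

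**Conclusion.** The point holds in a limited form. Under 5.6.2.2 and 5.9.2, a week-8 PASI-50 responder who loses at least half of the improvement at week 12 or 16 and is back below that threshold at week 20 is counted as not relapsed. This follows from the text and needs no assumption.

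A reader might go further and infer that every re-treated patient is scored as not relapsed, that both arms' rates are necessarily too low, or that the rule favours the herbal arm. The documents support none of these. Relapse is still counted when re-treatment fails. No re-treatment rate, success rate or arm difference is given, so the size of any understatement and the direction of any bias are unknown. The fall from 40% to 30% or 20% illustrates 25% or 50% masking and is not an estimate.

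Severity is minor: a secondary outcome of a pilot, with a cheap improvement available.

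**What to change.** In 5.6.2.2 and the synopsis, define relapse among week-8 PASI-50 responders as whichever comes first of:

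- loss of at least 50% of the baseline-to-week-8 PASI improvement at any of weeks 12, 16 or 20;
- start after week 8 of a new therapy given for psoriasis, taken from the concomitant medication record with psoriasis as the indication. Herbal therapy counts. Antimicrobials and other drugs given for another condition do not.

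Report the cumulative proportion by week 20 and the visit at which relapse occurred. Keep the week-20 PASI-only status as a supporting result. Amend 5.9.2 so that week-12 and week-16 data are used for this outcome. This is a counting rule and does not bear on which treatment patients receive in follow-up.

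Cost: a change of wording, with no new visit or PASI assessment. The case report form must show the indication for each concomitant drug; the protocol does not say whether it does. The reported rate will be higher, partly because three visits give more chances to cross the threshold than one. Therapy started without a 50% loss will also count as relapse, so the PASI-based and therapy-based components should be reported separately.
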